## Abstract

Chronic diseases remain one of the most pressing public health challenges in Europe, disproportionately affecting older adults and residents of rural and underserved areas. Structural barriers to healthcare access, insufficient social support networks, and fragmented service delivery models amplify health disparities in these communities. In response, proximity-based and integrated care models have emerged as promising strategies, especially under national initiatives such as Italy’s National Recovery and Resilience Plan (PNRR). The CAMP (Chronic health Assessment and Mapping of Proximity needs) study is a cross-sectional, observational, non-interventional protocol designed to identify and characterize the unmet health and social care needs of adults living with chronic conditions in rural areas of Southern Italy. Using a mixed-methods approach, the study integrates standardized quantitative tools—the SF-36, EQ-5D, Barthel Index, and MSPSS—with semi-structured interviews to assess quality of life, functional autonomy, access barriers, and perceived social support. The study population includes adults aged ≥18 years with at least one chronic condition, recruited through general practitioners and social services. Descriptive and multivariate analyses will be used to explore associations between clinical and social variables, while thematic analysis will be applied to qualitative data. Expected outcomes include a comprehensive mapping of service gaps and resource distribution, as well as feasibility assessments for implementing community hospitals and telemedicine models. The findings will inform evidence-based territorial health planning and contribute to shaping more equitable and integrated care strategies for vulnerable populations. This protocol was preregistered on the Open Science Framework on May 26, 2025 (DOI: https://doi.org/10.17605/OSF.IO/YHD87).

## Introduction

Chronic non-communicable diseases (NCDs) are among the leading causes of morbidity, disability, and premature death worldwide [1]. Their burden is growing steadily, particularly in high-income and ageing societies such as Italy [2], where the prevalence of chronic conditions is exacerbated by sociodemographic transitions and structural inequalities. In rural and semi-rural contexts, limited availability of services, geographic isolation, and workforce shortages further amplify health disparities and complicate disease management [3,4].

Beyond the Italian context, recent European and OECD reports underline how unmet health and social care needs represent a persistent challenge across countries. The Health at a Glance: Europe 2024 report highlights that ageing, multimorbidity, and territorial disparities are straining healthcare systems, especially in rural areas with limited infrastructure [5]. Similarly, the OECD volume Does Healthcare Deliver? Living with Multiple Chronic Conditions (2025) emphasizes that people with multimorbidity experience poorer health outcomes, fragmented care pathways, and significant barriers to accessing integrated primary and community-based services [6].

Empirical studies confirm these trends. For instance, Maslyankov et al. (2024) documented that in Bulgaria a significant share of chronically ill adults reported unmet needs related to long waiting times, transportation difficulties, and affordability [7]. In Finland, Ilmarinen et al. (2024) found that, despite a well-developed welfare state, older adults and patients with chronic conditions continue to face obstacles related to costs, distance, and transport [8]. Comparative analyses across European countries have also shown that both formal and informal long-term care remain insufficient, leaving many individuals without adequate support [9].

Recurring themes include logistical barriers (distance, transport), economic constraints, fragmented services, and insufficient psychosocial support. These patterns reinforce the need for a mixed-methods approach: while quantitative tools capture the prevalence and distribution of unmet needs, qualitative inquiry allows exploration of patient perspectives, lived experiences, and expectations regarding service delivery. This dual perspective is particularly valuable for tailoring integrated and proximity-based care interventions, as called for by Italy’s National Recovery and Resilience Plan (PNRR) [10].

The CAMP (Chronic health Assessment and Mapping of Proximity needs) study was designed to respond to this gap. It focuses on adults living with chronic conditions in underserved areas of Southern Italy and aims to map their health-related quality of life, functional autonomy, perceived social support, and difficulties in accessing healthcare and social services. By combining quantitative tools with qualitative narratives, the study will generate data to inform place-based care planning, support the feasibility of proximity interventions, and guide policymakers toward more responsive and equitable chronic care strategies.

This manuscript outlines the protocol of the CAMP study, detailing its design, methodology, and expected contributions to both research and practice in territorial health policy.

## Materials and methods

### Aim, design and setting of the study

The CAMP study (Chronic health Assessment and Mapping of Proximity needs) is designed as a cross-sectional, observational, non-interventional study employing a mixed-methods approach. It will be conducted in multiple rural and semi-rural municipalities within the Campania region of Southern Italy, in collaboration with local health authorities and social services. For the purposes of this study, underserved rural/semi-rural areas are defined as municipalities with a medium/low population density (<150 inhabitants/km²), located more than a 30-minute drive from the nearest tertiary care hospital, and with below-average availability of health and social services, based on regional planning indicators. The classification also considers additional socioeconomic vulnerability factors, such as population aging and per capita income below the regional average. These operational criteria ensure transparency and replicability in the selection of recruitment areas.

The primary aim is to assess the health and social care needs of adults with chronic conditions residing in underserved areas, to inform future proximity-based care planning.

### Sample size, inclusion and exclusion criteria

The sample size was calculated assuming a 30% prevalence of patients reporting significant barriers to healthcare access, with a 5% margin of error and 95% confidence level. This prevalence was adopted as a conservative assumption, consistent with recent European evidence reporting unmet healthcare needs in the range of 25–35% among chronically ill and rural populations [5; 7,8]. Considering a potential dropout or non-response rate of 20–25%, we aim to enroll approximately 400–500 participants.

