## Expected results

The CAMP study is expected to produce a comprehensive dataset describing the clinical, functional, and social characteristics of adults with chronic illnesses residing in rural and semi-rural Southern Italy. We anticipate identifying a high prevalence of unmet needs in areas such as health-related quality of life, access to services, and perceived social support. It is expected that older age, lower education level, and geographic remoteness will be significantly associated with worse outcomes on SF-36 and Barthel Index scores.

The study also anticipates that a notable proportion of participants will report difficulties in accessing health services, with long waiting times, travel distances, and limited domiciliary support emerging as key barriers. Thematic analysis of qualitative data is expected to yield recurring patterns related to care fragmentation, lack of service integration, and caregiver burden.

These findings will allow the generation of territorial maps indicating service gaps and population clusters most at risk, thus supporting the planning of localized interventions such as the implementation of community hospitals, multidisciplinary teams, and telemedicine services.

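### The 30% planning prevalence is the midpoint of the plan's own 25–35% range, not a conservative value, and the lower enrolment bound of 400 misses ±5 points at the stated 25% loss

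*Protocol article*

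**What the plan says.** The section on sample size, inclusion and exclusion criteria of the protocol article bases the study size on the precision of one proportion. The calculation is made "assuming a 30% prevalence of patients reporting significant barriers to healthcare access", "with a 5% margin of error and 95% confidence level". The choice of 30% is justified in the next sentence: "This prevalence was adopted as a conservative assumption, consistent with recent European evidence reporting unmet healthcare needs in the range of 25–35" per cent. The enrolment target follows: "Considering a potential dropout or non-response rate of 20–25%, we aim to enroll approximately 400–500 participants". The number of completers behind that target is not printed, so it has to be recomputed from these inputs.

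**The concern.** Two statements in this paragraph do not fit its own figures.

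First, the variance of a proportion, p(1−p), grows as p approaches 50%. In a precision calculation the cautious choice within a range lying wholly below 50% is its upper end. The plan took the middle and called it conservative, which tells the reader that the margin is protected against the less favourable values in the cited evidence. It is not.

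Second, the target is a range of enrolment numbers paired with a range of loss rates. A reader will take it that any enrolment in 400–500 delivers the 5% margin at any loss in 20–25%. At the lower enrolment bound and the higher loss rate this is not so.

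At stake is the accuracy of the stated precision for the prevalence of access barriers. Enrolment near 400 is conceivable: the section on participant characteristics and sample selection itself acknowledges practical barriers to recruitment.

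**Working it through.** **Inputs**, all from the sample size section: p = 0.30, cited range 0.25 to 0.35; margin d = 0.05, read as absolute percentage points; 95% confidence, z = 1.96; loss L = 0.20 to 0.25; enrolment N = 400 to 500. Simple random sampling is assumed, with no design effect and no finite-population correction.

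**Step 1. Completers needed**, n = z²p(1−p)/d², rounded up:

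- p = 0.25: 1.96² × 0.1875 / 0.0025 = 288.1, so 289
- p = 0.30: 1.96² × 0.2100 / 0.0025 = 322.7, so 323
- p = 0.35: 1.96² × 0.2275 / 0.0025 = 349.6, so 350

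The requirement rises across the plan's own range, and 30% sits in the middle of it.

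**Step 2. Enrolment needed**, N = n/(1−L), rounded up:

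| Prevalence | Completers | Enrolled, 20% loss | Enrolled, 25% loss |
|---|---|---|---|
| 25% | 289 | 362 | 386 |
| 30% | 323 | 404 | 431 |
| 35% | 350 | 438 | 467 |

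The 30% row reproduces the plan's target: 404 to 431 lies within approximately 400–500.

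**Step 3. Margin achieved at the two ends of the target**, z√(p(1−p)/m) with m = N(1−L):

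| Enrolled | Loss | Completers m | p = 25% | p = 30% | p = 35% |
|---|---|---|---|---|---|
| 400 | 20% | 320 | ±4.74 | ±5.02 | ±5.23 |
| 400 | 25% | 300 | ±4.90 | ±5.19 | ±5.40 |
| 500 | 20% | 400 | ±4.24 | ±4.49 | ±4.67 |
| 500 | 25% | 375 | ±4.38 | ±4.64 | ±4.83 |

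At 400 enrolled, 30% prevalence and 20% loss, the Wilson half-width is ±5.00, so the ±5.02 is a matter of rounding. At 25% loss the Wilson half-width is ±5.16, so that shortfall does not depend on the interval method.

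**Step 4. Check of the two possible floors.** With 431 enrolled and 25% loss, m = 323.25 and the margin at 30% is ±5.00; at 35% it would be ±5.20. With 467 enrolled and 25% loss, m = 350.25 and the margin at 35% is ±5.00, with smaller margins at 30% and 25%.

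**The case against.** The strongest reply is that the calculation reproduces. The stated inputs give 404 to 431 enrolled, inside the stated target, and the target is worded as approximate. This stands, and it rules out the reading that the sample size has failed: 500 enrolled keeps the margin below 5 points over the whole cited range at either loss rate. The range even contains the 438 to 467 needed at 35%.

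A second reply is that the gap is small. It is 0.02 points at 30% prevalence and 20% loss, 0.19 points at 25% loss, and at most 0.40 points within the plan's own range. At 25% prevalence there is no gap. This also stands, and it limits the weight of the point. Recruitment through GPs and social services, with snowball sampling where appropriate, makes differences of this order uncertain in any case.

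Third, conservative might be meant loosely, as a moderate figure. But the word describes the assumption in a precision calculation, and 30% is not the cautious end of 25–35% in either direction.

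Three stronger readings are tempting but not supported:

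- A reader might infer that prevalence will exceed 35%, because the expected results section says "We anticipate identifying a high prevalence of unmet needs". That sentence covers several domains, access among them, and gives no figure. Margins computed at 50% therefore lie outside the plan's cited evidence and do not show a miss.
- A reader might infer that the loss allowance is misapplied because non-responders are never enrolled. The study procedures section lets people who have already consented complete data collection at a later appointment. Non-response after enrolment is possible, and inflating the enrolment number for it is coherent.
- A reader might infer that the study will stop at 400. No such rule is given; recruitment is planned by calendar dates, with a possible extension.

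**Conclusion.** The point holds as a wrong description of the planning assumption and a lower bound set somewhat too low. Within 25–35% the conservative prevalence for a margin of error is 35%, which takes 350 completers, 27 more than the 323 at 30%. At the assumed 30%, enrolling 400 meets ±5 points at 20% loss for practical purposes but not at 25% loss, where 431 are needed, 31 more than the lower bound. The worst margin within the plan's own ranges is ±5.40 points.

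The effect is small, but the correction is worth making because it concerns a precision that the article states outright. The result rests on reading the 5% as absolute points, on applying the whole 20–25% loss after enrolment, and on simple random sampling. Clustering by practice or municipality would widen the margins, but the article gives no intraclass correlation, so no figure is offered.

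**What to change.** Either of two changes to the sample size paragraph is enough.

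1. Delete the word conservative, call 30% the midpoint of the cited range, and state that the margin may be up to about ±5.4 points if only 400 are enrolled (35% prevalence, 25% loss).
2. Replace the range by one enrolment floor and give the number of completers behind it: at least 431 enrolled (323 completers) if 30% is kept, in which case the word conservative should still go; or at least 467 enrolled (350 completers) with planning at 35%, which holds ±5 points across 25–35% at up to 25% loss.

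In both cases, say that the figures assume simple random sampling. The cost is one paragraph. The first option makes the stated margin slightly less favourable; the second raises the floor by 31 or 67 participants but stays inside the existing 400–500. Neither changes the design.

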### Inclusion criteria

Age ≥ 18 years;

Clinical diagnosis of one or more chronic diseases (e.g., COPD, diabetes, heart failure, chronic kidney disease, dementia);

Registered with a general practitioner (GP) in the selected territories;

Ability to provide informed consent (directly or with caregiver assistance).

### Exclusion criteria

Current hospitalization or acute clinical instability;

Severe cognitive impairment without caregiver support, assessed on the basis of an existing clinical diagnosis documented in medical records or confirmed by the general practitioner. In doubtful cases, GP clinical judgment will be used to exclude patients who are unable to provide informed consent or actively participate in data collection;

Refusal to participate.

### Characteristics of participants and sample selection

Eligible participants will be identified through GP registries and social service records in the participating municipalities. There is no randomization or blinding, given the observational nature of the study. Recruitment will be coordinated by GPs and social workers, who will provide information sheets and collect written informed consent. We acknowledge that GP workload and the difficulty of reaching the most isolated individuals may represent practical barriers to recruitment. To mitigate these challenges, additional strategies will be implemented, including outreach activities through community organizations, collaboration with municipal health coordinators, and the use of snowball sampling when appropriate. These measures aim to maximize recruitment feasibility and ensure the inclusion of hard-to-reach populations.

### Study procedures and outcomes

This study does not include any interventions, experimental treatments, or comparison arms. It solely involves administering validated questionnaires and conducting interviews. After providing written informed consent, participants will be offered the choice to complete data collection either immediately at the GP’s office or social services site, or at a later scheduled appointment with the research team. Quantitative questionnaires and qualitative interviews may be administered during the same session or, when more convenient for the participant, in separate encounters within a two-week period. While the preferred mode is face-to-face, flexibility is ensured through the availability of telephone or videoconference options, particularly for participants residing in remote areas or with mobility limitations. These procedures aim to maximize feasibility, inclusiveness, and adherence across diverse rural settings.

**Quantitative data** will be gathered using the following validated instruments:

SF-36: to assess health-related quality of life [11].

EQ-5D: to measure health status and utility [12].

Barthel Index: to evaluate functional autonomy in activities of daily living [13].

MSPSS: to assess perceived social support [14].

**Qualitative data** will be collected through semi-structured interviews focused on patients’ experiences with care access, perceived needs, and expectations [15]. For the qualitative component, a purposive subsample of approximately 40–50 participants will be selected to ensure diversity in age, sex, type of chronic condition, and degree of geographic isolation. Interviews will be conducted until thematic saturation is reached, defined as the point at which no new codes or themes emerge from successive interviews. The semi-structured interview guide will include broad thematic areas such as: (i) experiences and barriers in accessing healthcare and social services; (ii) perceptions of care coordination and integration; (iii) psychosocial and family support needs; (iv) expectations and suggestions for proximity-based care models (e.g., community hospitals, telemedicine). The final wording of questions may be refined following piloting, but these domains directly reflect the study objectives and gaps identified in the literature on unmet needs among rural populations.

The primary and secondary outcomes of the study are summarized in Table 1.

**Table 1 pone.0335196.t001:** Primary and secondary outcomes of the study.

Type	Outcome	Measurement tool/ Source
**Primary**	Unmet health and social care needs	Semi-structured interviews; survey questionnaire
	Health-related quality of life	SF-36, EQ-5D
	Functional autonomy	Barthel Index
	Perceived social support	MSPSS
**Secondary**	Access barriers	Survey items; qualitative narratives
	Service gaps mapping	GP/social services reports; patient responses
	Feasibility of proximity-based care	Survey items; qualitative interviews

### Data management

All data will be anonymized and entered into a secure electronic database with controlled access, compliant with EU GDPR regulations. Data will be stored for at least 5 years following study completion.

### Safety considerations

No interventions or experimental treatments will be performed. Participants will only complete questionnaires and interviews, ensuring minimal risk.

### Statistical analysis

Descriptive statistics (means, SDs, frequencies) will summarize participant characteristics. Bivariate analyses (t-tests, ANOVA, chi-square) will explore associations among clinical and social variables. Multivariable logistic and linear regression models will identify predictors of poor quality of life, reduced autonomy, and limited access to care. Qualitative data from interviews will be analyzed using thematic analysis with independent coders to ensure triangulation. The study will adopt a sequential explanatory mixed-methods design. Quantitative analyses will first provide prevalence estimates and associations between clinical, functional, and social variables. Subsequently, qualitative interviews will be used to contextualize and deepen the understanding of these findings. Integration will occur at the interpretation stage through triangulation, whereby themes emerging from the qualitative analysis will be compared and contrasted with quantitative results to identify convergences, divergences, and complementarities. This approach ensures that the qualitative strand enriches the quantitative findings, providing a more comprehensive understanding of unmet needs in rural chronic care.

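### The ±5-point margin makes no allowance for clustered recruitment, and the named bivariate tests assume independence, which matters most for predictors that vary between areas

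*Protocol article*

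**What the plan says.** The section on sample size and eligibility bases the calculation on a single proportion, "assuming a 30% prevalence of patients reporting significant barriers to healthcare access", "with a 5% margin of error and 95% confidence level". It then allows for loss: "Considering a potential dropout or non-response rate of 20–25%, we aim to enroll approximately 400–500 participants". It mentions no design effect, ICC or number of clusters.

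The recruitment structure is described elsewhere. On the setting: "It will be conducted in multiple rural and semi-rural municipalities within the Campania region of Southern Italy". On sampling: "Eligible participants will be identified through GP registries and social service records in the participating municipalities", supplemented by "the use of snowball sampling when appropriate". The setting section qualifies areas by municipality, using drive time to tertiary care, population density and service availability.

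The Statistical analysis section names the bivariate tests: "Bivariate analyses (t-tests, ANOVA, chi-square) will explore associations among clinical and social variables". It adds multivariable logistic and linear regression, without a variance method. The Expected results section anticipates that older age, lower education and "geographic remoteness will be significantly associated with worse outcomes on SF-36 and Barthel Index scores".

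**The concern.** People in the same municipality, or on the same GP's list, share services, travel distances and staff. These are plausible determinants of the outcome that drives the sample size, namely barriers to access. Snowball referral can add further similarity between participants. A positive correlation within clusters means that each extra person from the same cluster adds less information than the formula assumes.

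Two things are at stake. The prevalence interval would be reported as narrower than the data justify. And a test comparing areas would be compared with the wrong standard error, because t-tests, ANOVA and chi-square in their usual form treat every participant as an independent unit. The second point matters here because the study is meant to produce territorial maps of service gaps and expects remoteness to be a significant predictor.

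**Working it through.** **Inputs from the article.** Prevalence p = 0.30, margin d = 0.05, 95% confidence (z = 1.96), loss 20–25%, enrolment 400–500.

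**Inputs that are assumptions.** Cluster size m, number of municipalities and ICC. The article gives none of them, so ranges are shown.

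**1. Reproducing the plan's figure.** n = z²p(1−p)/d² = 1.96² × 0.30 × 0.70 / 0.05² = 322.7, so 323 analysed. Dividing by 0.80 and 0.75 gives 404 and 431 enrolled. The lower end of 400–500 is therefore the independence formula plus loss, and the upper end is rounding up. No design effect is needed to reach the target.

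**2. Slack in the target without clustering.** Margin = 1.96 × √(0.21/n). Slack is the largest design effect that still keeps the margin at 5 points, n/322.7.

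| Enrolled | Loss | Analysed | Margin, no clustering | Largest design effect for ±5 |
|---|---|---|---|---|
| 400 | 20% | 320 | ±5.02 | 0.99 |
| 400 | 25% | 300 | ±5.19 | 0.93 |
| 500 | 20% | 400 | ±4.49 | 1.24 |
| 500 | 25% | 375 | ±4.64 | 1.16 |

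At the low end there is no slack. At the high end, with 20 per cluster, the slack is used up at an ICC of (1.24 − 1)/19 ≈ 0.013 or (1.16 − 1)/19 ≈ 0.009.

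**3. Margin with clustering.** Design effect = 1 + (m − 1) × ICC; margin = 1.96 × √(0.21 × design effect / n).

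| m | ICC | Design effect | Margin, 323 analysed | Margin, 400 analysed |
|---|---|---|---|---|
| 10 | 0.01 | 1.09 | ±5.2 | ±4.7 |
| 10 | 0.05 | 1.45 | ±6.0 | ±5.4 |
| 20 | 0.02 | 1.38 | ±5.9 | ±5.3 |
| 20 | 0.05 | 1.95 | ±7.0 | ±6.3 |
| 30 | 0.05 | 2.45 | ±7.8 | ±7.0 |

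**4. Type I error for a predictor that is constant within a municipality.** With about 320 people, a nominal 5% test that ignores clustering has a true error of about 2[1 − Φ(1.96/√design effect)].

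| Municipalities × people | ICC | Design effect | Effective n | Type I error |
|---|---|---|---|---|
| 20 × 16 | 0.02 | 1.30 | 246 | 9% |
| 20 × 16 | 0.05 | 1.75 | 183 | 14% |
| 10 × 32 | 0.02 | 1.62 | 198 | 12% |
| 10 × 32 | 0.05 | 2.55 | 125 | 22% |

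Simulating a plain two-sample t-test on null data (normal outcomes, half of the municipalities in each group) gives the same values to within about one percentage point.

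**The case against.** Several objections have force.

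- **The regressions.** A reader might infer that every planned analysis ignores clustering. The article does not support that. It names logistic and linear models without a variance method, and random intercepts or robust standard errors could stand in a fuller plan that is not shown. For the models this is silence. Only the sample size calculation and the bivariate tests are stated in a form that assumes independence, and those tests are described as exploratory.
- **P-values in general.** Two of the three expected predictors, age and education, are person-level. Where a predictor varies mainly within clusters, the inflation is smaller and can be absent or even reversed.
- **Remoteness.** Treating it as a municipality-level variable is an inference from how the areas are defined. The Study procedures and outcomes section uses degree of geographic isolation to select individual interviewees, so it may vary within a municipality, which would lessen the inflation.
- **Effective sample size.** It is tempting to say that for remoteness the effective sample size is close to the number of municipalities. That is wrong at these ICCs: it is about 125–246 in the scenarios above. The number of municipalities limits the degrees of freedom.
- **Fixed municipalities.** If inference is meant only for the participating municipalities, they act as strata and add no design effect to the prevalence estimate. The Discussion mentions stratified sampling, though the section on sample selection describes none. Even so, dependence within GP practices and referral chains would remain, and the Discussion also claims generalizability.
- **Consequences.** The study is descriptive, and a margin a point or two wider does not defeat a mapping of needs.

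These objections narrow the point and lower its severity. They do not remove the mismatch between the stated precision and the stated recruitment.

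**Conclusion.** The point holds in limited form. The ±5 margin is a simple-random-sampling figure attached to a clustered, partly snowball sample. At 400 enrolled it is marginally missed even without clustering, so any positive ICC widens it further. At 500 enrolled it survives only a small design effect. For 20 per cluster and ICC 0.02–0.05, a realistic statement would be about ±5.9 to ±7.0 points with 323 analysed, or ±5.3 to ±6.3 with 400.

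Unadjusted p-values would be too small mainly for predictors that vary chiefly between areas. The 9–22% error range applies to a plain t-test on a predictor fixed within each of 10–20 municipalities, at ICC 0.02–0.05.

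The direction of the problem follows from the article whenever the ICC is positive. Its size rests on an assumed ICC, cluster size and number of clusters, so confidence in the size is medium. This should be fixed, but it does not threaten the study's descriptive purpose.

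**What to change.** **In the sample size section:** state that ±5 points holds under simple random sampling, and give the margin after clustering for an explicit range of assumed ICC and cluster size, labelled as assumptions. The sample need not be enlarged.

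**In the Statistical analysis section:**
- Keep coded municipality and GP-practice identifiers in the anonymized dataset. If anonymization strips them, no later adjustment is possible.
- Compute prevalence intervals with cluster-robust variance.
- Specify random-intercept models, or cluster-robust standard errors with a small-sample correction, and cluster-adjusted versions of the bivariate tests. This matters above all for remoteness, which should be judged against variation between municipalities if it is measured at that level.

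**Cost:** some wording and one or two coded fields, which are easiest to settle before data collection; the article reports that recruitment had not begun at submission. Intervals will be wider and the stated margin somewhat less favourable. No extra participants are needed.

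### The plan is labelled sequential explanatory, but its timing, interviewee selection and integration describe a convergent design; label and procedure should be reconciled

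*Protocol article*

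**What the plan says.** The two descriptions are both in the current text of the protocol article.

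**Statistical analysis** names the design and spells out its order: "The study will adopt a sequential explanatory mixed-methods design. Quantitative analyses will first provide prevalence estimates". The same analyses are to examine how the study variables are associated. The interviews come next in the text: "Subsequently, qualitative interviews will be used to contextualize and deepen the understanding of these findings". The same paragraph places integration at interpretation, where themes are set against quantitative results to see where they agree, differ or complement each other.

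**Study procedures and outcomes** sets out the fieldwork:
- **Start** (at the consent visit, or by arrangement with the research team): "participants will be offered the choice to complete data collection either immediately at the GP’s office or social services site, or at a later scheduled".
- **Spacing of the strands:** "qualitative interviews may be administered during the same session or, when more convenient for the participant, in separate encounters within a two-week period".
- **Interviewees:** a purposive subsample of about 40–50, "selected to ensure diversity in age, sex, type of chronic condition, and degree of geographic isolation".
- **Interview guide:** four thematic areas drawn from the study objectives and the literature on unmet needs. Wording may be refined after piloting.

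**Study status and timeline** gives recruitment from September to December 2025, one data-collection period to March 2026, a possible extension to June 2026, and results in June–July 2026. It mentions no interim quantitative analysis and no separate qualitative phase.

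**The concern.** The plan's own definition of its design puts quantitative *analyses*, not merely questionnaires, ahead of the interviews, and gives the interviews the task of explaining what those analyses show. That order has a practical purpose: the results decide whom to interview and what to ask. The fieldwork rules leave no room for it. A team that follows Study procedures and outcomes will run a different study from the one declared under Statistical analysis.

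This matters because semi-structured interviews are a named source for the primary outcome of unmet needs and for two of the three secondary outcomes in Table 1. If the quantitative results are unexpected or discordant (for example, high reported barriers with good perceived support), the plan has no means of interviewing people chosen to explain them. A publication calling the design explanatory would claim more than the procedure supports. Once interviews have been held, the sequence cannot be restored. At manuscript submission recruitment had not begun.

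A smaller matter is that the order within a shared session is not stated. An interview about access barriers held before the questionnaires could colour the answers to them.

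**Working it through.** **1. Declared design against stated procedure**

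| Feature | Needed for the declared order | What the article sets |
|---|---|---|
| Timing | Cohort-level analysis before interviews | Same session, or within two weeks |
| Choice of interviewees | Informed by quantitative results | Age, sex, condition, isolation; no questionnaire result |
| Interview content | Adapted to the findings to be explained | Objectives and literature; refined only after piloting |
| Integration | Results feed into the interview phase | At interpretation only |
| Timeline | Cut-off, analysis, then interviews | One data-collection period, no interim analysis |

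All five features fit two strands collected side by side and compared at the end.

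**2. How often could an interview follow cohort-level data?**

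The dates come from Study status and timeline and the 14-day window from Study procedures and outcomes. Assumptions of this check: recruitment runs from 1 September to 31 December 2025 (121 days), enrolment is uniform, and data collection starts at consent.

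- Share of participants whose window closes before the last enrolment: (121 − 14)/121 = 107/121 = 88%.
- If questionnaires are instead spread evenly to 31 March 2026 (121 + 90 = 211 days): (211 − 14)/211 = 197/211 = 93%.

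The remainder is 14/121 = 12% or 14/211 = 7%. With interviewees spread evenly as well, that is roughly 3 to 6 of the 40–50 (from 40 × 14/211 = 2.7 to 50 × 14/121 = 5.8). Even these few could be interviewed after an analysis only if one were run within days of the last questionnaire, and none is planned.

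**3. Ceiling for the order-of-administration issue**

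Interviewees as a share of the enrolment target: 40/500 = 8% to 50/400 = 12.5%. This is an upper limit, reached only if every interviewee were interviewed before completing the questionnaires.

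**4. The plan's own sample size**

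n = 1.96² × 0.30 × 0.70 / 0.05² = 322.7, rounded up to 323. Allowing for non-response, 323/0.80 = 404 and 323/0.75 = 431. Both lie within the stated 400–500, so the target is reproduced. It does not depend on the mixed-methods label.

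**The case against.** The strongest reply is that the passage sits under Statistical analysis and says interviews will be *used* subsequently, not *conducted* subsequently. Read that way, only the order of analysis is meant, and it is compatible with concurrent collection. The reading is possible, but the text does not state it. On that reading the explanatory label is still wrong, because nothing in the sampling or the guide depends on quantitative results.

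Second, same-session interviews are permitted, not required, and the later appointment has no stated limit. This stands as far as it goes. A reader might infer from the two-week rule that no interview at all could be informed by any quantitative result. The documents do not support that: someone enrolled late, or given a late appointment, could be interviewed after earlier participants' data had been examined. But the only alternative offered to a shared session is still bounded at two weeks, and no such examination is planned.

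Third, contextualising remains possible. This is right. A reader might infer that the interviews cannot illuminate the associations at all, but the article plans exactly that comparison at interpretation. What is lost is targeted follow-up.

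Fourth, order within a session is operational detail that an article may leave to the full protocol, and the article mentions questionnaires before interviews. This also stands. Contamination of the questionnaire outcomes is a possibility, not something the documents show.

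The reply that an article condenses a fuller document does not dispose of the main point, which is a conflict between two statements that are both present.

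**Conclusion.** The point holds as a mismatch between the declared design and the stated procedure. As written, the study is convergent in substance. Themes can be compared with quantitative results afterwards, but for nearly all participants neither the choice of interviewees nor the questions can be built on cohort-level findings. The 88–93% figure rests on uniform enrolment and a two-week window running from each participant's first data collection. The conclusion does not hang on its exact value, because no analysis is scheduled before interviews in any case.

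Priming is a possible risk only, in at most 8–12.5% of participants. The sample size, the questionnaire outcomes and the regression models are untouched, and a change of wording cures the main defect. It should be fixed, but it does not threaten the quantitative results.

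**What to change.** Reconcile Study procedures and outcomes, Statistical analysis, and Study status and timeline by one of two routes.

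**Route 1 (cheapest): match the label to the procedure.** Call the design convergent, remove *first* and *subsequently*, and limit the claim to triangulation at interpretation. The cost is wording and a more modest claim.

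**Route 2: keep the explanatory claim.** Take interviews out of the same-session and two-week rule. Set a questionnaire cut-off and a preliminary quantitative analysis. Select the 40–50 interviewees and adapt the guide on those results, then interview within the period to March 2026 or the stated extension to June 2026. The costs are:
- a second contact for 40–50 people;
- a retained pseudonymised linkage key, since Data management says all data will be anonymised and people cannot be selected on their answers and recontacted without one;
- a questionnaire closing date earlier than March 2026, which the timeline does not now contain; using the extension would also press on the June–July 2026 results date.

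Under the Discussion's own commitment, protocol amendments go to the Ethics Committee and the OSF registry. That reporting should be budgeted for, especially under Route 2.

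**Under either route,** add one sentence requiring all questionnaires to be completed before the interview begins. This costs nothing and removes the possible priming.
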